## Abstract

**Background:**

Stress-related illnesses constitute a huge problem in society. The primary care services in Sweden form the first line of care whose role is to coordinate interventions for reducing symptoms, as well as health-promoting interventions. There is lack of knowledge concerning health-promoting interventions for these illnesses. The aim of this study is to evaluate whether photo-supported conversations about well-being (Be Well™) as an intervention, in addition to care as usual within the primary care services, improves health and well-being for patients with stress-related illnesses. The intervention will be compared to a control group, who receive care as usual. A further aim is to conduct a process evaluation.

**Methods/Design:**

This ongoing project has a quasi-experimental design, using quantitative and qualitative methods, and includes patients from primary care centres in two Swedish counties. Seventy patients, 20–67 years, with stress-related illnesses will be recruited. They constitute an intervention group, which receive the intervention together with care as usual, and a control group, which receive care as usual. The intervention, photo-supported conversations about well-being, involves 12 sessions. Care as usual entails medication, occupational therapy, physiotherapy and/or psychotherapy. Data collection is carried out at baseline, and outcomes are assessed directly after the intervention, as well as six months after completion of the intervention. The outcomes are evaluated based on factors related to health, well-being and everyday occupations. Furthermore, data concerning experiences of well-being and perceptions of the intervention will be collected in interviews. The therapists will also be interviewed about their experiences of performing the intervention. Data will be analysed with non-parametric statistics, and qualitative methodology.

**Discussion:**

The project is based on the concept that focusing on well-being despite living with stress-related illness may positively impact health and well-being as well as activity-related aspects, and that photo-supported conversations about well-being can contribute a complement to other treatment and rehabilitation. A strength is the use of a wide range of methods: such as quantitative measures, photographs, and qualitative interviews with participants and therapists. The results will thus provide knowledge about potential effects of this health-promoting intervention.

*Trial registration* Clinical Trials.gov: NCT04832295; retrospectively registered 2nd April 2021 https://clinicaltrials.gov/ct2/show/NCT04832295

## Background

Public health is generally good in Sweden, but despite that it has been reported that levels of well-being are lower [1]. Mental health issues, such as symptoms of depression, anxiety and/or stress, are also increasing internationally [2] and cause large societal costs [3]. Stress-related illness constitutes a major problem [4], in particular due to the large numbers. Symptoms of stress can entail e.g. exhaustion, cognitive problems and poor sleep, which in turn reduce well-being and the capacity to manage activities in the everyday life of those affected [5].

The importance of combating mental health issues in people in working age has been emphasized [2]. Primary care interventions exist, e.g. behavioral and multimodal interventions [6] and occupational therapy interventions aimed at lifestyle changes, and skill-building to promote health [7]. Patients with stress-related disorders may also be offered interventions, e.g. group treatment programs to facilitate changes in everyday life [8], nature-based interventions to facilitate the reduction of symptoms of stress [9], or interventions focusing on work rehabilitation [10, 11].

The primary care services form the first line of care in Sweden, and according to Swedish Government, they should coordinate not only interventions for reducing symptoms, but also focus on interventions, which are health-promoting, preventive and rehabilitative, in order to increase the health of the population [12].

This study protocol presents a health-promoting intervention focusing on improving health and well-being as well as on activity-related aspects among people with a diagnosed stress-related disorder, by addressing their well-being and what contributes to this from their own perspective. The present intervention originates from a pilot project designed by the research group “Finding viability in daily life, experiences of well-being despite stress-related illness” [13, 14] using photo elicitation as a visual research method. Previous research has found visual research methods useful in relation to complex phenomenon [15, 16], such as well-being. Pictures present more and other information than words do [17] and allowing the participants to photograph by themselves has been described as to “capture the world through the participant’s eyes” (18, p.1).

The results in our previous pilot project [13, 14], with twelve women with stress-related illness, showed that experiences of taking photographs and talking about well-being in their everyday life, based on these photographs, was considered valuable as it redirected the participants towards a focus on their well-being [14]. Furthermore, it was found that well-being was perceived as an unconditional beingness, when the participants did not have to perform or meet any demands. A supportive environment was found to be important for promoting well-being, while some participants developed their own strategies to achieve the same aim [13].

The pilot project did not aim to be therapeutic, but positive feelings about participation and the usefulness of taking photographs and talking about them, were described. However, participants also described a need for continued training based on the new focus on well-being.

In summary, the results of the pilot project indicated that using photographs for reflecting about well-being in everyday life, despite suffering from stress-related disorders, was perceived as useful. The promising results inspired us to evaluate whether an intervention based on photo-supported conversations about well-being, conducted over time for increased training, could be beneficial as a health-promoting supplement to care as usual. Such a type of intervention, as a complement to stress rehabilitation programs, might be useful for health professionals working with people suffering from stress-related disorders or at risk for this.

However, the pilot project only consisted of one occasion for reflections about wellbeing based on photographs, and we have no knowledge about the potential outcomes of a health-promoting intervention consisting of several sessions. We thus want to investigate patients’ self-rated health and well-being, activities in everyday life, and potential improvements from a quantitative as well as qualitative perspective. This study protocol concerns a health-promoting intervention for the intervention group, named Be Well™, based on photo-supported conversations aiming to improve health and well-being, and focusing on quantitative as well as qualitative outcomes, compared with a relevant control group.

## Methods

### Aim

The aim of this study is to evaluate whether photo-supported conversations about well-being (Be Well™) as an intervention, in addition to care as usual within the primary care services, improves health and well-being for patients with stress-related illnesses. The intervention will be compared to a control group, who receive care as usual. A further aim is to conduct a process evaluation.

The research questions related to the quantitative evaluation are:How are the participants’ health and well-being affected by photo-supported conversations?oPrimary outcome is self-rated symptoms of exhaustion.pSecondary outcomes are self-rated, depression and anxiety, sense of coherence and quality of life.How are the participants’ activities in everyday life affected by the photo-supported intervention?oSecondary outcomes are self-rated balance of activities in everyday life and work ability.The research questions related to the qualitative evaluation are:How are the participants’ well-being and everyday life experienced and affected by photo-supported conversations?oHow do the participants perceive their well-being and everyday life, prior to and after the intervention?pHow can the photographs contribute to the understanding of well-being in everyday life?The research questions related to the process evaluation of the intervention Be Well™ are:How do the participants perceive their participation in the photo-supported conversations about well-being?How do the participants rate their client satisfaction?How do the therapists perceive the performance of photo-supported conversations about well-being?

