### The intervention

The intervention group received photo-supported conversations about well-being, i.e. the intervention Be-Well™, in addition to care as usual. The intervention has been developed on the basis of previous studies in the pilot project [13, 14], and on knowledge about health, well-being and everyday life activities [23, 24], and visual methodology [15].

The intervention is individually conducted, and the patients meet their occupational therapist (OT) physically and/or virtually for 12 sessions (intended to be conducted within 12 to 15 weeks). The intervention consists of three parts, sessions 1–4, sessions 5–10 and, sessions 11–12.

Sessions 1 to 4 are full-length 60-min meetings with the therapist. They were originally intended to be physical meetings but due to the Covid-19 pandemic they can also be switched to be virtual. The patient takes photographs of what they see as being related to their well-being prior to each of the sessions and sends 1–3 of these photographs to the OT before the session. The OT enlarges each of the photographs to the A4 size and brings them to the session. The conversation during the session is based on the photographs and the patient is encouraged to talk about each of them and how they relate to their well-being as well as the feelings or thoughts related to the photograph. Potential strategies for everyday life are discussed, e.g. to do more or less of an activity which relates to their well-being or solve a difficult activity in another way, and these strategies are tested between the sessions. Sessions 2 to 4 begin with a reflection on the last session before the new photographs are discussed.

Sessions 5–10 are short virtual meetings of approximately 15–20 min with the aim of following the patient, confirming their process and supporting them in their direction towards increased well-being. The patient continues photographing well-being, discusses these photographs shortly with their OT as well as their self-given homework to increase their well-being.

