### Data collection

Two researchers ([name], UH), and one project assistant collect the data for the intervention group and three project assistants collect data for the control group. The project assistants are OTs, who are not involved in the intervention. All project assistants have been informed about the project and its aim and the project leader will have continuous contact with them throughout the project to discuss progress and clarify potential issues. The project assistants also meet regularly to discuss together with the researchers and the therapists.

The intervention group meets the data collector prior to the start of the intervention; after the intervention; and 6 months after the performed intervention ended. The control group meets the data collector at the same time points as the intervention group (Fig. 1). In order to protect their confidentiality, all the participants received a code number when recruited, and the list linking names to code numbers is stored separately.

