#### Qualitative measures

Participants in the intervention group are interviewed individually on all data collections with open-ended questions [42] focused on their experiences of well-being in their present life situation and follow-up questions to gain a greater understanding of their life situation. Participants in the control group are interviewed individually during a shorter interview, focusing on their present life situation. Both groups are interviewed three times.

The interview *prior to the intervention* is related to the participant’s present situation in everyday life, and what causes stress at home and at work, and what contributes to well-being despite living with stress.

The interview *after the intervention* in addition to the same open-ended questions as prior to the intervention, also focuses on the participant’s experiences of the intervention to increase health, well-being and work ability. During this occasion, their photographs from the intervention are used as well and copies of the photographs are also handed over to the data collector as they are data.

The interview *six months after the intervention* focuses on the participant’s present life situation, as well as their perception of photo-supported conversations as intervention. The interview also focused on whether, and if so, how they have been able to use photographs in their everyday life to achieve well-being after the intervention ended.

Each interview is audio recorded and begins with open questions and the participant is encouraged to talk about how they achieve well-being in relation to their everyday life, by describing a certain situation or example. Follow up questions are used as well.

All therapists will, after the final participant, who is receiving their intervention has finished, also be asked to participate in an interview (individual and/or focus group) for investigating their experiences of the intervention, and how to improve the intervention in order to better suit clients with stress-related disorders.

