### Sample size

The power calculation for this study was based on the Karolinska Exhaustion Disorder Scale (KEDS) [26]. In a previous study where this instrument was used, the response within each subject group was normally distributed with standard deviation 8.74 [43]. It was thus anticipated that if the true difference in KEDS means (scale on 0–54) between the experimental and control is 7, we will need to study 29 experimental subjects and 29 control subjects to be able to reject the null hypothesis that the population means of the experimental and control groups are equal with probability (power) 0.8. As this study has several timepoints, it is likely that there will be dropouts from the study, and we will thus include a total of 35 experimental subjects and 35 control subjects. The Type I error probability associated with this test of this null hypothesis is 0.05.

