### Analysis

Non-parametric statistics will be used for investigating potential differences between the intervention and control groups in health, and activity-related variables as well as in client satisfaction since the instruments are based on nominal and ordinal scales. Missing data for dropouts will be estimated using the last data obtained before a participant dropped out. The transcribed interviews will be analysed for meanings using thematic [44] and phenomenological [42] analysis. The qualitative data will be analysed for meanings in accordance with the methodological principles of openness, flexibility and a reflective attitude. The analysis is a process defined by a movement between the whole and the parts, with the purpose of identifying a new whole in the phenomenological studies [42] and identifying themes of meanings in the thematic studies [44]. The photographs will be analysed with a semiotic method [45] regarding content and formal aspects, such as shape and color, perspective, spatiality and composition.

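### The process evaluation of Be Well is at risk of completer bias, probably upward: those who leave the study before the post-intervention visit are never asked about it, and carry-forward cannot supply their rating

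*Protocol article*

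**What the plan says.** All places are in the protocol article.

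- **Aim.** Two of the three process-evaluation questions concern participants' own views: "How do the participants perceive their participation in the photo-supported conversations about well-being" and "How do the participants rate their client satisfaction". The third concerns the therapists.
- **Data collection.** The intervention group is seen "prior to the start of the intervention; after the intervention; and 6 months after the performed intervention ended". No data-collection contact is stated during the 12 sessions, which are meant to take 12 to 15 weeks (The intervention).
- **Qualitative measures.** The baseline interview covers everyday life, stress and well-being. The post-intervention interview, "in addition to the same open-ended questions as prior to the intervention, also focuses on the participant’s experiences of the intervention", is the first to raise Be Well. The six-month interview raises it again.
- **Secondary outcomes.** The CSQ has eight items scored 1 to 4 and rates the treatment a patient has received. No time point is given for it.
- **Sample size.** "it is likely that there will be dropouts from the study, and we will thus include a total of 35 experimental subjects", against 29 needed.
- **Analysis.** Non-parametric comparisons between the groups cover the health and activity variables "as well as in client satisfaction since the instruments are based on nominal and ordinal scales". The next sentence replaces dropouts' missing data with their last available value, with no exception for any instrument.
- **Context and procedure.** Patients who decline before consent are asked for their reason where possible. Nothing equivalent is described for those who leave after starting.

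**The concern.** Be Well asks exhausted patients to take photographs repeatedly, test strategies and do homework between sessions. The Discussion itself warns that taking part in the research can be an added strain. Patients who leave because it is too much are the ones a process evaluation most needs to hear from, and the stated schedule does not reach them if they leave before the second visit.

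The carry-forward rule adds a separate difficulty. For KEDS, a baseline value is at least a measurement of the same quantity. For satisfaction with Be Well, no value obtained before the intervention can be a rating of it. A rule that is workable, if crude, for the other scales has no meaning for this one.

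At stake are the satisfaction scores and interview themes. They would be presented as the participants' view while resting on those who stayed, or, for the CSQ, while partly containing ratings of other care. The KEDS comparison is not affected by this point.

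**Working it through.** **Step 1. Who is asked about Be Well under the stated schedule?**

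| Situation | Asked about Be Well? | What carry-forward gives for the CSQ |
|---|---|---|
| Finishes the sessions, attends the post-intervention visit | Yes | Not needed at that visit |
| Stops the sessions, stays in the study | Possibly; no text excludes it | Not needed if the CSQ is completed |
| Leaves the study before the post-intervention visit | No | No value, or an earlier one about other care |
| Leaves between the post-intervention and six-month visits | Yes, once | The post-intervention rating, if the CSQ was taken then |

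Only the third row is certain to be missed.

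**Step 2. How many could that be?** The article gives 29 needed and 35 enrolled per group, and no dropout rate.

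- Allowance: 35 − 29 = 6, and 6/35 = 17.1%.
- This is a ceiling within the plan's allowance. The extra subjects are justified by the several time points, so the six include people lost after the post-intervention visit, who have already been asked.
- The 29 itself is not reproduced from the stated inputs (difference 7, SD 8.74, 80% power, 5% taken as two-sided). The normal formula gives 2 × (1.96 + 0.84)² × 8.74²/7² ≈ 24.5, so 25 per group. The t-test gives 26, and a Wilcoxon adjustment 27. The stated number errs on the safe side. It is used here only to read off the allowance.

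**Step 3. Size of a possible bias in the satisfied share.** If *c* of 35 are asked, with satisfied share *p* among them and *q* among those who left:

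- share among all starters = [c·p + (35 − c)·q]/35
- overstatement = p − that share = (35 − c)/35 × (p − q)

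The values of *p* and *q* are assumptions; the article gives none. With c = 29 and p = 90%:

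| Leavers satisfied (q) | All starters | Overstatement |
|---|---|---|
| 90% | (26.1 + 5.4)/35 = 90.0% | 0 points |
| 60% | (26.1 + 3.6)/35 = 84.9% | 5.1 points |
| 20% | (26.1 + 1.2)/35 = 78.0% | 12.0 points |
| 0% | 26.1/35 = 74.6% | 15.4 points |

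With p = 80% the range is 0 to 13.7 points. If only three leave early (c = 32), the maximum at p = 90% is 7.7 points. If nine do (c = 26, beyond the plan's allowance), it is 23.1 points.

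**Step 4. The same on the CSQ total.** If the eight items are summed (range 8 to 32; summing is assumed) and stayers average 28 (assumed), leavers' means of 28, 24, 20 and 16 give all-starter means of 28.0, 27.3, 26.6 and 25.9. The overstatement is 0 to 2.1 points.

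**Step 5. Direction.** Steps 3 and 4 apply when leavers have no CSQ value. If a baseline CSQ is taken and carried forward, the error depends on how satisfied leavers were with their other care, and its sign cannot be predicted.

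**The case against.** The strongest reply is that this is an omission in a condensed article. Exit procedures and reasons for withdrawal are usually set out in the full protocol, which is not shown, and the overview figure was not available for this review. No text rules out an exit contact. That stands, so the absence of an exit interview is not in itself the fault. What remains is what the article does fix: a schedule in which Be Well is first raised after the intervention, and a carry-forward rule applied without exception to a measure it cannot serve.

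Three stronger readings are tempting and are not supported:

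- *That satisfaction is rated only after the intervention.* The article gives no time point for the CSQ. The scale concerns received treatment and is compared between both groups, so it is not a rating of Be Well alone.
- *That everyone who stops Be Well early goes unheard.* Stopping the sessions and leaving the study are different events. The article speaks of dropping out of the study and does not exclude those who stop sessions from later visits.
- *That acceptability and satisfaction will be overstated.* Leavers' views are unknown, and people also leave for reasons unrelated to the programme. If leavers think as stayers do, there is no bias.

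It is also fair to say that the therapist interviews may bring in information about patients who left, and that improving the programme is the stated purpose of those interviews. They are second-hand, however, and answer the therapist question rather than the two about participants' own views. The therapists' session reports are tied to completed interventions, so they may not cover leavers either. Finally, the article plans no satisfied-percentage endpoint and interview themes do not estimate a proportion, so the shares in the working only illustrate scale.

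**Conclusion.** The point holds as a risk of completer bias, probably upward, confined to participants who leave the study before the post-intervention visit. For them the stated schedule yields no view of Be Well, and carry-forward yields either nothing or a rating of something else. The upward direction is a judgement: burden is a plausible reason for leaving, and the article itself raises strain.

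On the plan's allowance at most 6 of 35 (17%) are affected, and probably fewer, since that allowance also covers later losses. With an assumed 90% satisfaction among stayers, the overstatement lies between 0 and about 15 percentage points. The unsuitability of carry-forward for the CSQ does not depend on any assumed satisfaction value.

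**What to change.** 1. Exempt the CSQ from the carry-forward rule in the Analysis section.
2. State that participants who stop the sessions remain in the planned post-intervention data collection where they agree.
3. Offer those who leave the study a short, voluntary telephone or virtual exit contact: the CSQ with reference to the sessions attended, the reason for stopping, and a few of the open questions from the post-intervention interview. An existing project assistant who is not involved in the intervention should make it.
4. Report the CSQ and the interview themes separately for finishers and stoppers, with the number not reached.
5. State when the CSQ is given and which treatment each administration refers to.

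If the full protocol already provides for an exit contact, items 1, 4 and 5 are still needed.

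The cost is about six short calls at the plan's own allowance and a few sentences of text. Some leavers will refuse, and must be free to, so the gap will shrink rather than close. The satisfaction figure may become less favourable.
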